## Methods

### Design

The present investigation is a randomized, controlled, noninferiority, two-arm trial comparing the efficacy of different surgical approaches of RT on the oncology and fertility outcomes in Chinese patients with early-stage CC (Figs. 1 and 2). A total of 28 domestic centers will recruit 414 patients (207 per group) from December 31, 2018, to December 31, 2020. All the surgeries are to be performed by the specialists designated in the research center (the primary investigators are listed in Supplementary Table 1). The patients are randomized on the day of written consent obtainment by the random data website (http://random.your-data.cn:8095/random), which assigns each patient a randomization number. Specified surgeons from all centers are in charge of enrolling participants. When one potential eligible patient is enrolled, her information will be sent to [name], who will generate the allocation sequence and assign participants to interventions. The allocation, together with treatment information, will be discussed with the patient by her surgeons when patients attend the clinic to get results, and relevant informed consent will be signed. On the consent form, participants will be asked if they agree to the use of their data should they choose to withdraw from the trial. Participants will also be asked for permission for the research team to share relevant data with people from the universities taking part in the research or from regulatory authorities, where relevant. This trial does not involve collecting biological specimens for storage. Model consent form and other related documentation given to participants and authorized surrogates are available from the corresponding author on request.

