### Secondary objectives and secondary endpoints

The secondary objectives are as follows:
To evaluate the OS at the 5-year follow-upTo assess different strategies of RT in terms of fertility and obstetric outcomesTo compare the incidence of perioperative complications of different surgical approachesTo compare major perioperative complications within 28 days after surgery and major postoperative complicationsTo determine the general and specific QoL

Secondary endpoints will therefore be the following:
All-cause mortalityFertility outcomes consisting of cervical incompetence, natural pregnancy, and infertility treatment such as intrauterine insemination or IVF-ET; obstetric outcomes consisting of the time interval between the RT surgery and pregnancy; the overall mean length of time during which conception was attempted; the number of pregnancies; the mode of delivery; and the outcome of each pregnancy, such as spontaneous abortion, induced abortion, drug abortion, preterm birth, premature rupture of membranes, fetal growth restriction, and full-term birthPerioperative complications consisting of injury of the ureter, bladder, bowel, blood vessels, or nerves, and vaginal bleeding, and postoperative complications consisting of postoperative pelvic infection, pelvic lymphocele, intrauterine infection, Asherman syndrome, abnormal menstruation, urinary tract infection, hydronephrosis, intestinal obstruction, chronic pain, varices at the site of uterovaginal anastomosis, and fistula formationMajor perioperative and postoperative complications consisting of early postoperative complications (cerebrovascular, pulmonary, and renal diseases; ileus; abdominal wound complications; septicemia; thromboembolism; and lymphocele formation and secondary infection) and delayed postoperative complications (lymphedema, vaginal evisceration)QoL assessment comprising the authorized Chinese edition of EORTC QLQ-C30 [13] and its CC module QLQ-CX24 [14], the 19-item Female Sexual Function Index (FSFI) [15], and the PFIQ-7 questionnaire [16].

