### Description of statistical methods

#### Sample size calculation

Systematic reviews have revealed that the rate of disease recurrence after ART is 3.8 to 4.7% [10, 19]. The 5-year DFS of ART in a Chinese study was 96.5% [20]. In our study, we assume that the recurrent rate of ART of 5 years is 5%. A noninferiority log-rank test with an overall sample size of 331 subjects (165 in the reference group and 166 in the treatment group) achieves 90.1% power at a 0.050 significance level to detect an equivalence hazard ratio of 0.75 when the actual hazard ratio is an equivalence hazard ratio of 1.00, and recurrence rates of 5 years in the MIRT and ART group are 7 and 5% [21]. Considering the possible 20% rate of loss to follow-up, 414 patients are needed to accomplish the study goal.

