#### Statistics

Continuous variables conformed to the normal distribution will be described with means and standard deviations, and discrete variables not conformed to the normal distribution will be summarized with medians, ranges, and interquartile ranges. The *t* test will be used for continuous variables, and the chi-square test or Fisher’s exact test will be used for categorical variables. To evaluate the strength of associations, bivariate and multivariable logistic regression analyses will be used, and the strength of associations will be expressed as hazard ratios (HR) with 95% confidence intervals (95% CI). Kaplan-Meier plots will be generated for recurrence and death rates between the groups, and the log-rank test will be applied for the eventual significant differences. The survival outcomes will be compared according to intention to treat and per protocol. The analysis of intention to treat is available for protocol nonadherence. These statistical analyses will be performed using SPSS 22.0 (SPSS Inc., Chicago, IL, USA). All analyses will be two-sided, and significance will be set at a *P* value of 0.05.

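### Per-pregnancy obstetric outcomes fall under tests that assume independent observations, which makes their standard errors too small if pregnancies are the unit tested

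*Protocol article*

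**What the plan says.** Women are randomised individually (Design: "414 patients (207 per group").

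Among the secondary endpoints (Secondary objectives and secondary endpoints), some obstetric items are defined at the level of the pregnancy: "the outcome of each pregnancy, such as spontaneous abortion, induced abortion, drug abortion, preterm birth", followed by further categories up to full-term birth. The same list includes "the number of pregnancies; the mode of delivery", so more than one pregnancy per woman is expected.

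The Statistics section then sets one rule for all categorical data: "the chi-square test or Fisher’s exact test will be used for categorical variables". For associations, "bivariate and multivariable logistic regression analyses will be used". Sidedness and level are common to everything: "All analyses will be two-sided, and significance will be set at a" P value of 0.05. The section names no method for repeated observations on the same woman, and it does not say whether the woman or the pregnancy is the unit for obstetric outcomes.

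**The concern.** Chi-square, Fisher and ordinary logistic regression all require independent observations. Two pregnancies in the same woman share the same operation, the same residual cervix and the same surgeon, so losses and preterm births plausibly cluster within women. If pregnancies are entered as separate observations, a woman with repeated losses counts as if she were several women. The variance is then understated, and a difference between the minimally invasive and abdominal arms is declared significant too often.

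Obstetric outcome is part of the trial's stated purpose. A spurious difference in miscarriage or preterm birth could influence how young women and their surgeons choose the approach.

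**Working it through.** **Inputs from the protocol article.** Two-sided significance level 0.05 (Statistics). Outcome recorded for each pregnancy, several per woman possible (Secondary objectives and secondary endpoints).

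**Inputs that are assumptions.** The article gives no number of pregnancies per woman and no within-woman correlation (ICC). Main scenario: among conceiving women, 60% have one pregnancy, 28% two and 12% three. The ICC ranges from 0.05 to 0.5.

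**Formulas.**
- Size-weighted mean number of pregnancies: m_w = Σm² / Σm
- Design effect: DEFF = 1 + (m_w − 1) × ICC
- Actual two-sided error of the uncorrected test: α* = 2 × [1 − Φ(1.96 / √DEFF)]

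**Baseline.** With one pregnancy per woman, or ICC = 0, DEFF = 1 and α* = 5.0%, the level that the article states.

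**Main scenario.**
- Mean = 0.60×1 + 0.28×2 + 0.12×3 = 1.52
- Mean of m² = 0.60×1 + 0.28×4 + 0.12×9 = 2.80
- m_w = 2.80 / 1.52 = 1.84

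| ICC | DEFF | 1.96/√DEFF | Actual error |
|---|---|---|---|
| 0.05 | 1.04 | 1.92 | 5.5% |
| 0.2 | 1.17 | 1.81 | 7.0% |
| 0.3 | 1.25 | 1.75 | 8.0% |
| 0.5 | 1.42 | 1.64 | 10.0% |

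Beta-binomial simulation of this scenario (80 conceiving women per arm, event rate 30% in both arms, both assumed) gives 10.0% at ICC 0.5. A cluster-robust test on the same kind of data stays at about 5 to 6%.

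**Sensitivity to the number of pregnancies.** A separate simulation used 50 pregnant women per arm and an event rate of 35%, again assumed, with 20,000 replicates. Rejection rates of the uncorrected test:

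| Mean pregnancies (share with 1/2/3/4) | m_w | ICC 0.1 | ICC 0.3 | ICC 0.5 |
|---|---|---|---|---|
| 1.25 (80/15/5/0%) | 1.48 | 5.4% | 6.8% | 7.7% |
| 1.5 (60/30/10/0%) | 1.80 | 5.8% | 7.9% | 9.7% |
| 2.0 (35/35/25/5%) | 2.40 | 6.8% | 10.1% | 13.2% |

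The simulations agree with the formula. Spread in the number of pregnancies matters as well as the mean. Setting m to 1.5 for every woman would give only 6.8% at ICC 0.3 and 8.0% at ICC 0.5, because that ignores the extra weight of women with several pregnancies.

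**The case against.** The strongest reply is that the defect is inferred. The sentence on categorical variables is generic and names neither an endpoint nor a denominator. Recording the outcome of each pregnancy does not oblige anyone to pool pregnancies. A chi-square test on one value per woman, such as first pregnancy or any full-term birth, would be valid, and Table 1 collects pregnancy wishes and outcomes per patient every 12 months. The unit of analysis for a secondary endpoint is often left to a statistical analysis plan, and none is shown.

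Part of this stands. A reader might infer that the article commits itself to testing pooled pregnancies; it does not say so. The point therefore holds only for a literal application of the rule. It is still more than missing detail: the section assigns a test to every categorical variable without exception, and that rule does not fit an endpoint which the article itself defines per pregnancy.

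A reader might also infer a single headline inflation, such as 12%. The documents support no such figure. An error of 12% needs a design effect of about 1.59, for example three pregnancies per woman with ICC 0.3, or two with ICC 0.6. A mean alone does not fix it: at mean 1.75 made up of 25% with one and 75% with two pregnancies, m_w = 3.25/1.75 = 1.86, so ICC 0.5 gives DEFF 1.43 and about 10%. Nor is 12% a ceiling, since three pregnancies per woman at ICC 0.5 gives 16.6%. The size can only be shown as a range under stated assumptions.

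**Conclusion.** The concern holds in a limited form. The Statistics section, applied as written to outcomes defined per pregnancy, uses tests whose independence assumption those data do not meet, and the direction of the error is known if within-woman correlation is positive. The inflation is slight when that correlation is small and reaches about double the nominal level only when it is strong (about 0.5 at roughly 1.5 pregnancies per conceiving woman) or when women have more pregnancies. All of these sizes rest on assumed pregnancy counts and correlations.

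A reader might extend the point to fertility results as a whole or to the main result. The documents do not support either. Natural pregnancy, infertility treatment, cervical incompetence and the count of pregnancies can each be analysed as one value per woman. The primary disease-free survival comparison uses one observation per randomised woman, and the sample size rests on that endpoint alone, so neither is touched by this point. It is a secondary-endpoint correction, worth making because it is cheap.

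**What to change.** In the Statistics section, exempt outcomes defined per pregnancy from the chi-square/Fisher rule. Compare them with a generalised estimating equation, or a cluster-robust variance, with the woman as cluster.

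Add a per-woman comparison of at least one full-term birth, with every randomised woman counted once. This keeps the randomised groups intact, whereas a per-pregnancy rate describes only women who conceived.

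Do not make at least one pregnancy loss or at least one preterm birth, over all randomised women, the main comparison. Both rise with the number of pregnancies, so the arm with better conception could look worse.

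The cost is a sentence or two of text. No extra patients or data are needed, because pregnancy outcomes are already collected woman by woman, and the GEE procedure in SPSS can be used if that software is kept. Confidence intervals for per-pregnancy rates widen by about √DEFF: in the main scenario roughly 2% at ICC 0.05 (√1.04), 8 to 12% at 0.2 to 0.3 (√1.17 to √1.25) and 19% at 0.5 (√1.42).

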## Discussion

In our study, we have enrolled women younger than 40 years, with stage IA1 disease with LVSI, stage IA2, and smaller stage IB1 tumors (≤ 2 cm diameter); without evidence of lymph node metastases on imaging; with evidence of endocervical extension on MRI; and with a desire to preserve fertility. At present, five different FSS procedures are available for patients with CC: conization, a simple trachelectomy, VRT, MIRT (including laparoscopic and robot-assisted routes), ART, extraperitoneal RT (a novel fertility-preserving option) [23], and neoadjuvant chemotherapy (NACT) followed by FSS (conization/simple trachelectomy or RT). MIS has gained wide acceptance secondary to the implied advantages of a faster return to normal activity and diet, reduced hospital stay and postoperative discomfort, and decreased scarring and rate of adhesive. Although the open approach is more radical in terms of parametrial and paracervical resection [10], it has theoretical drawbacks, particularly the formation of adhesions and scar tissue that may ultimately impact a woman’s fertility, increased blood loss, and a prolonged hospital stay.

Additionally, with the advent of the sentinel lymph node procedure, the morbidity in this usually young patient population has continued to improve. There are adequate data to prove that oncologic outcomes, concerning recurrence and mortality, are comparable to those of RH and that the obstetrical outcomes are favorable [17]. However, a recent study has put forward contrasting conclusions; thus, we aim to evaluate the impact of different surgical approaches of RT on survival and obstetric outcomes.

One of the crucial designs is the consideration of the learning curves of surgeons. A learning curve is defined by the number of surgical procedures performed by a surgeon before he or she reaches an accepted plateau in objective outcomes such as operative time, estimated blood loss (EBL), complication rate, and surgical performance [24]. Research defining learning curves in gynecologic oncology surgery is limited but has shown that gynecologic oncology surgeons can become proficient after 20 cases of robotic hysterectomy with pelvic-aortic lymph node dissection and that their performance can be continually improved in the period between 50 and 70 cases [25]. Compared with vaginal RT, ART has a shorter learning curve, requires minimal additional training, and has a higher oncological radicality. ART is similar to the abdominal RH procedure that most gynecologic oncologists are familiar with [26–28]. This suggests that experience is critical in laparoscopic and robotic procedures [29]. However, there is little literature about the learning curve for MIRT. Therefore, each study center would appoint only one specific expert who will manage all the major procedures of RT, and their quality would be evaluated by the amount and survival outcomes of the surgeries.

### Trial status

Recruitment of participants started in December 2018, and the last participant is expected to reach the primary endpoint (5-year follow-up) in December 2025. Primary data analysis will begin in December 2023. The naturalistic follow-up phase of the trial will continue until December 2025. The protocol version number and date were 3.0 and December 23, 2018, respectively.

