### Main objective and primary endpoint

The primary objective of the analysis is to evaluate the 5-year DFS related to different surgical approaches for radical trachelectomy (RT). The primary endpoint will be recurrence confirmed by imaging or histology.

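### The primary analysis is dated December 2023, two years before the last participant completes the 5-year follow-up that the primary objective needs

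*Protocol article*

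**What the plan says.** Four statements in the protocol article bear on the timing.

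- **Main objective and primary endpoint:** the primary objective is to "evaluate the 5-year DFS related to different surgical approaches".
- **Design:** the centres "will recruit 414 patients (207 per group) from December 31, 2018, to December 31, 2020".
- **Trial status, end of 5-year follow-up:** "the last participant is expected to reach the primary endpoint (5-year follow-up) in December 2025". The article itself thus equates the primary endpoint with 5 years of follow-up.
- **Trial status, analysis:** "Primary data analysis will begin in December 2023", followed by "The naturalistic follow-up phase of the trial will continue until December 2025".

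The Sample size calculation section is also built on 5-year recurrence: 5% after the abdominal procedure (ART) and 7% after the minimally invasive one (MIRT). The article describes no interim analysis, event-driven trigger or other reason for the earlier date.

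**The concern.** The plan fixes a 5-year primary objective, dates the completion of 5-year follow-up to December 2025, and then dates the primary analysis two years earlier. An analysis plan could not simply fill this in, because it is a stated date that conflicts with the stated time horizon.

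Three things are at stake.

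1. A 5-year DFS estimate from a December 2023 data cut would depend on a Kaplan-Meier tail with hardly any women at risk.
2. The trial expects few recurrences, and about a fifth of those due within 5 years would not yet have occurred. In a noninferiority comparison of a cancer operation, late recurrences are part of the outcome of concern, and they would fall outside the primary result.
3. If the sponsor instead tests again in 2025, there are two looks at the primary hypothesis and no error control is described.

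The second and third are alternatives and do not add up. As written, the text also leaves open which of the two dates yields the trial's conclusion.

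**Working it through.** **Inputs from the protocol article.** Recruitment from 31 December 2018 to 31 December 2020 and 414 women (Design); 5-year completion in December 2025 and primary analysis from December 2023 (Trial status); 5-year recurrence of 5% (ART) and 7% (MIRT) (Sample size calculation).

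**Assumptions, not in the article.** Uniform accrual, constant hazard, no loss to follow-up, and a data cut in December 2023.

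**Step 1: reproduce the article's own date.** Last entry 31 December 2020 + 5 years = 31 December 2025. This agrees with the stated December 2025. The gap to December 2023 is two years.

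**Step 2: follow-up in December 2023.** With a cut on 31 December 2023, the last woman has 3.0 years, the first 5.0 years, and the median is 4.0 years. The number with a full 5 years depends on the exact days, because Trial status gives only the month in which recruitment began:

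| First entry | Data cut | Follow-up (years) | Women with 5 years, of 414 |
|---|---|---|---|
| 31 Dec 2018 | 1 Dec 2023 | 2.92 to 4.92 | 0 |
| 31 Dec 2018 | 31 Dec 2023 | 3.00 to 5.00 | about 1 |
| 1 Dec 2018 | 1 Dec 2023 | 2.92 to 5.00 | about 1 |
| 1 Dec 2018 | 31 Dec 2023 | 3.00 to 5.08 | about 17 (4%) |

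**Step 3: recurrences already seen.** For a 5-year recurrence p, the hazard is λ = −ln(1 − p)/5. The expected proportion recurred at the cut is the mean of 1 − exp(−λt) for t uniform on 3 to 5 years.

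- p = 0.05: λ = 0.01026 per year; mean = 0.0402; 0.0402/0.05 = 80%.
- p = 0.07: λ = 0.01451 per year; mean = 0.0564; 0.0564/0.07 = 81%.

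Events among 414 women, against everyone followed for exactly 5 years:

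- 5% in both arms: 414 × 0.0402 = 16.6, against 414 × 0.05 = 20.7.
- 5% and 7%: 207 × (0.0402 + 0.0564) = 20.0, against 207 × (0.05 + 0.07) = 24.8.

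**Step 4: dependence on the constant hazard.** Keep 5% at 5 years but let the hazard follow a Weibull form. Shape 0.5 (early recurrences) gives 89% seen by December 2023; shape 1.5 (late recurrences) gives 73%. The shortfall is therefore 11% to 27%, with 20% for a constant hazard.

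**Step 5: error rate if the test is repeated in 2025.** Take two unadjusted looks at information fraction 0.8, so the test statistics have correlation √0.8 = 0.894. The chance that at least one exceeds the critical value c is 1 − P(Z₁ < c, Z₂ < c).

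- c = 1.960 (one-sided 0.025): 0.035.
- c = 1.645 (one-sided 0.05): 0.069.

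Both are shown because the Sample size calculation section does not say whether its 0.050 level is one- or two-sided. The Statistics section makes all analyses two-sided at 0.05, which is closer to the first.

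**The case against.** The strongest reply has four parts.

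- **The text says only that analysis will begin in 2023.** It gives no data cut and does not call this the noninferiority test, so the work could start then and finish after December 2025. That reading is possible, but the article does not state it. It sets the primary analysis apart from a follow-up phase that continues to 2025, which reads as follow-up after the primary analysis. December 2023 is also 5 years after first entry, so the date may have been counted from the first participant; that is an inference, and it would still need correcting.
- **The log-rank test and hazard ratio use censored follow-up.** This stands: a comparison in 2023 would be possible. It would not supply the 5-year result that the objective and the sample size refer to.
- **The lost events barely change power.** This also stands. With a margin of 0.75, a true hazard ratio of 1.00 and equal arms, power is Φ(½√D × |ln 0.75| − c). At c = 1.645, D = 16.6 gives 14% and D = 20.7 gives 16%. Power is low at either date for a separate reason, the sample size itself. The case for waiting rests on the 5-year horizon and on having a single fixed analysis, not on a gain in power.
- **No second test is planned, so error inflation is hypothetical.** Correct. The figures in Step 5 apply only if the comparison is repeated.

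**Conclusion.** The point holds, and the plan is wrong as written. The two-year conflict follows from the article's own dates and needs no assumption. That almost no women would have 5 years of follow-up also follows from the dates: none or about one of 414 under the stated recruitment window, and at most about 17 if recruitment began on 1 December 2018 and data are cut on 31 December 2023.

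The share of events seen, about 80% (range 73% to 89%), rests on uniform accrual, no loss to follow-up and the assumed hazard shape. A 2023 comparison by hazard ratio would be feasible, but it could not support the stated 5-year objective. This must be fixed, because the data cut for the confirmatory analysis is a core element of the design.

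**What to change.** In Trial status, state that the single confirmatory DFS analysis uses a data cut after the last participant has completed 5 years, expected in December 2025. Then delete the December 2023 primary analysis, or relabel it as a descriptive report at a minimum of about 3 years of follow-up, with no noninferiority claim. If December 2023 was meant only as the start of preparatory work, say so. If the sponsor does want a formal test in 2023, it has to be prespecified as an early look with its share of the error rate.

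The change is one sentence. The confirmatory result comes up to two years later, but follow-up to December 2025 is already planned, so no extra visits or patients are needed.
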